### **D.3.3 Baseline Data Collection**

We will collect baseline data from all participating clinics. Subjects will be eligible for medical record abstraction if they were seen at one of the participating clinics within one year of the clinic’s start in the project and if the subject has a breast or colorectal screening abnormality that meets eligibility criteria (see above). Specific data elements that will be collected are listed in the NOVA data dictionary (Breast - Table 7, Colorectal -Table 9).

Questions to be addressed using baseline data include:

*1. What is the average length of time from abnormal screening test to definitive diagnosis?*

*2. Are there any predictors of timeliness of diagnosis?*

For patients diagnosed with cancer, the following additional questions will be addressed.

*1. How many breast and colorectal cancers are diagnosed each year?*

*2. At what stage are these cancers diagnosed?*

*3. What is the average length of time from abnormal screening test to definitive diagnosis?*

*4. What is the average length of time from diagnosis to initiation of definitive treatment?*

*5. For each treatment modality (surgery, radiation therapy, chemotherapy), what percentage of patients is recommended to have treatment and what percent complete this therapy?*

*6. What physicians/ facilities currently provide diagnostic and cancer care?*

Baseline data will be helpful in establishing baseline estimates of project outcomes, confirming sample size requirements, and suggesting navigation strategies. Chart abstractions will be conducted on the clinic premises and no information that could uniquely identify a patient will be recorded. Thus the final dataset will be de-identified for human subjects purposes.

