**D.4.7.b Statistical Analysis and Study Power**

The statistical analyses will focus on those subjects receiving an abnormal or suspicious mammogram (BIRAD 0, 4, or 5) and those with abnormal FOBTs or abnormalities detected on sigmoidoscopy (see D.2.1). Those in the Navigator intervention groups will be compared to those in the control groups with respect to two outcomes. For patients with breast or colorectal abnormalities, the primary outcome will be time from detection of abnormality to definitive diagnosis, measured as a continuous variable. In addition, we will assess the proportion of patients who successfully complete an appropriate diagnostic evaluation. The records of each subject with such an indication for follow-up will be examined as described in D.3.3.

Study power is based on the following factors. The primary endpoint is ‘Length of time’ (LOT=time from screening to definitive diagnosis). Suppose LOT follows a normal distribution (mean=30 days, “std” = standard deviation). Then, to detect the difference in LOT between two groups (navigator versus control groups), a two-sample t-test will be used. The required minimum sample size to achieve 80% statistical power is calculated based on the t-test and illustrated in Figure 1.

For example, group sample sizes of 29 and 29 (total 58) achieve 80% power to detect a difference of 10 days between the null hypothesis that both group means are 30.0 and the alternative hypothesis that the mean of Navigator group is 20 days with estimated group standard deviations of 15.0 each and with a significance level of 0.05 using a one-sided two-sample t-test. However, to detect a difference of 5 days with the same standard deviation 15.0 between the two groups, one would need at least 112 samples for each group (total 224).

Figure 1. Required sample sizes for each group based on the expected mean of navigator group by the standard deviation. For the control group, the mean value of LOT was set up as 30.0. The standard deviations for both groups are assumed to be equal. α=0.05 (one sided: mean 1 > mean 2).

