Although we do not expect attrition of clinics, we have assessed power the possibility of between 6 and 8 participating clinics enrolling about 100 subjects each (a total of 600 - 800 subjects). Depending on the intracluster correlation coefficient (ICC) and the design effect, however, there may be effectively fewer subjects enrolled in this study from a statistical perspective. Assuming the intracluster correlation coefficient (ICC) to be in the range of 0.01 through 0.04, the effective sample sizes will be obtained as follows,

| # of total clinics | Actual Sample Sizes | ICC | Design Effect | Effected Sample Sizes |
| --- | --- | --- | --- | --- |
| 8 | 800 | 0.01 | 1.99 | 402 |
| 6 | 600 | 0.01 | 1.99 | 302 |
| 8 | 800 | 0.02 | 2.98 | 268 |
| 6 | 600 | 0.02 | 2.98 | 201 |
| 8 | 800 | 0.04 | 4.96 | 161 |
| 6 | 600 | 0.04 | 4.96 | 121 |

Therefore, given our expected sample sizes (600-800 subjects) even under the most conservative conditions (low design effects or ICC values, and relatively high population standard deviation), we will expect the desired statistical power will be achieved.

We will also conduct a number of secondary analyses in an exploratory fashion. For those with a suspicious screening result, we will compute the Kaplan-Meier curves for time from the suspicious result to definitive diagnosis (positive or negative) for each randomized arm. For those with positive diagnoses, we will compute Kaplan-Meier curves for time to onset of therapy for each randomized arm from both suspicious screening result and definitive diagnosis. In each case, we will estimate the standard error of these estimates with Greenwood’s formula and produce 95% confidence bands for these curves using the method of Hall and Wellner. The log rank test will be used to compare the two randomized groups. These comparisons will be at the two-sided 0.05 significance level.

Degree of adherence to NCCN standards will be assessed by an independent assessor blinded with respect to randomized arm and rated as 1 = complete adherence, 2 = substantial adherence, or 3 = poor adherence. The two randomized arms will be compared with respect to these adherence ratings using Wilcoxon’s Rank Sum Test.

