Risks: A concern could be raised that a loss of privacy could occur during the focus group (Phase I) if personal information is shared with others. In Phase II, the unit of randomization is at the clinic level and thus subjects in the control group will not be receiving the patient navigator intervention. However, patients at all clinics do receive follow-up and tracking of abnormalities through existing protocols according to their established standards of care. However, in consideration that this intervention could be efficacious, we do plan to offer the Patient Navigation Program to all sites after the initial evaluation has been conducted in the first two years. Thus, all patients at all sites will be exposed to the Patient Navigation Program at some point during the project.

Minimization: Within focus groups, all participants will be told at the start of the focus groups that information shared within the group should remain within the group. Subject data will be available only to research staff involved in this project. Data will be kept in locked filing cabinets in locked research rooms. Identifying information will not be reported. With regard to patients who are randomized to the control group, they will continue to receive standard care and outreach and follow-up, which is part of the standard protocols at the community-based centers. Once evaluated under controlled conditions, the Patient Navigation Program will be offered at all sites.

Risk: Exchange of information from one institution to another (Moffitt Cancer Center and the community-based centers).

Minimization: All data exchanged electronically from one institution to another and among team members will be in aggregate form with no identifiers.

Risk Chart abstractions conducted at six months or 12 months follow-up may identify patients for whom recommended care has not yet been received.

Minimization: Research assistants will compile listings of all patients for whom chart abstractions suggest that recommended care has not been received. These listings will be forwarded to the patient’s primary physician for review. Information that will be forwarded will include patient’s name, medical record number, and a listing of the targeted health services that were recommended but not received according to information obtained in the medical record abstraction.

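### The blanket power claim for 600–800 subjects fails for the plan's own 5-day difference in three of six table rows, and elsewhere depends on an SD of 15 days

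*Protocol*

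**What the plan says.** All of this is in Protocol D.4.7.b unless noted.

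- The model is stated as a supposition: "Suppose LOT follows a normal distribution (mean=30 days". The only SD printed in the text is 15 days in each arm. The test is a t-test on mean days, with "α=0.05 (one sided: mean 1 > mean 2".
- The first worked example is "group sample sizes of 29 and 29 (total 58) achieve 80% power to detect a difference of 10 days", "with estimated group standard deviations of 15.0 each and with a significance level of 0.05 using a one-sided two-sample t-test". The second, for a 5-day difference at the same SD, gives 112 per group, 224 in total.
- A table turns 6 or 8 clinics of about 100 subjects each into effective sizes for ICCs of 0.01, 0.02 and 0.04. They run from 402 down to 121.
- The conclusion drawn is that power is secure even in the most conservative case, described as low design effects or ICCs together with a "relatively high population standard deviation), we will expect the desired statistical power will be achieved". No difference and no SD is attached to it.
- Section D.3.3 adds: "Baseline data will be helpful in establishing baseline estimates of project outcomes, confirming sample size requirements, and suggesting navigation strategies". Section E.1.1 anticipates 700 such charts.
- Sections D.2 and D.4.3 put the current number of clinics at 12 (seven intervention, five control). Section E.1.1 allows up to 1,600 Phase II subjects.

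**The concern.** The table and the second worked example stand within a few lines of each other, and the conclusion does not compare them. Half of the effective sizes are smaller than the 224 that the 5-day example requires. The description of the conservative case also runs the wrong way for the ICC: a low ICC gives a small design effect and a large effective sample.

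The rows that do pass rely on an SD of 15, taken from a normal model that suits a waiting time poorly. Waiting times are bounded at zero and are usually right-skewed. The protocol follows charts to 12 months (D.4.1) and treats finishing the work-up as something that not everyone does: "In addition, we will assess the proportion of patients who successfully complete an appropriate diagnostic evaluation". A t-test on mean days gives each late resolution its full weight in the variance, so the SD is the input most likely to be too small.

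What is at stake is the reading of a null result. A reader who trusts the claim would take it as evidence against a 5-day gain, when power for that gain may have been well under 80%.

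**Working it through.** **Reproducing the plan.** With a one-sided 0.05 two-sample t-test, SD 15 and 80% power, the approximation is n per arm = 2 × SD² × (1.645 + 0.842)² / d².

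- d = 10: 2 × 225 × 6.18 / 100 = 27.8; the exact noncentral t gives 29.
- d = 5: 2 × 225 × 6.18 / 25 = 111.3; the exact noncentral t gives 112, or 224 in total.
- Design effect = 1 + 99 × ICC = 1.99, 2.98 and 4.96. Dividing 800 and 600 by these gives 402, 302, 268, 201, 161 and 121.

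All the printed figures are reproduced.

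**Joining the two parts.** This uses the same test with equal arms, and the effective size in place of the sample size, as the plan does. The last column of the table needs an assumption that the documents do not supply; it is explained below.

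| Clinics, ICC | Effective N | Power, 5 days, SD 15 | Detectable difference at 80%, SD 15 | Largest SD giving 80% for 5 days | Power, 5 days, illustration (SD 21.2) |
|---|---|---|---|---|---|
| 8, 0.01 | 402 | 95.5% | 3.7 days | 20.1 | 76.4% |
| 6, 0.01 | 302 | 89.3% | 4.3 days | 17.4 | 65.7% |
| 8, 0.02 | 268 | 85.9% | 4.6 days | 16.4 | 61.2% |
| 6, 0.02 | 201 | 76.1% | 5.3 days | 14.2 | 51.0% |
| 8, 0.04 | 161 | 67.8% | 5.9 days | 12.7 | 44.0% |
| 6, 0.04 | 121 | 57.1% | 6.8 days | 11.0 | 36.2% |

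Three rows fail for 5 days with nothing added to the plan's inputs. For 10 days at SD 15, every row has at least 97% power.

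**How plausible is Normal(30, 15)?**

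- Share below zero days: P(Z < −30/15) = 2.3% of controls, and P(Z < −20/15) = 9.1% of navigated patients at mean 20.
- Share beyond 90 days: P(Z > 60/15) = 0.00003.
- Share beyond 180 days: P(Z > 150/15) = 8 × 10⁻²⁴.

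**Illustration of a right tail (assumed inputs).** Suppose a share p in each arm resolves 150 days later than the rest, with the 5-day difference and the ICC unchanged. The SD is then √(225 + p(1 − p) × 150²).

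- p = 0.5%: SD 18.4, 336 needed for 5 days, best row 86%.
- p = 1%: SD = √(225 + 222.75) = 21.2, 446 needed, and power as in the last column. Simulating the mixture at 201 per arm gives 77%, against 76.4% from the formula.
- p = 2%: SD 25.8, 662 needed, best row 62%.

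For 10 days, p = 1% needs 114, so every row holds (83% at 121). At p = 2%, 168 are needed, and the rows of 161 and 121 fall to 79% and 68%.

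**Current clinic count.** Twelve clinics of 100 give 1,200 / 1.99 = 603, 1,200 / 2.98 = 403 and 1,200 / 4.96 = 242. Power for 5 days at SD 15 is 99%, 95.5% and 83%. The largest SDs that keep 80% are 24.7, 20.1 and 15.6.

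**The case against.** **No difference is named in the claim.** This is true, and for 10 days at SD 15 the claim is sound in every row. But the 5-day difference is the plan's other worked example, and an unqualified claim covers it.

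**The trial is now larger.** This stands as far as it goes. With 12 clinics of 100 and SD 15, all three ICCs give more than 80% for 5 days. At the 1,600 ceiling (133 per clinic) the effective sizes are 689, 439 and 254, with at least 84% power. The claim is nevertheless written for 600 to 800 subjects, and at ICC 0.04 with 12 clinics of 100 the margin is only from SD 15 to SD 15.6.

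**SD 15 is an example.** Figure 1 varies the SD and is not in the text available, so one cannot say that larger SDs went unconsidered. The closing claim still gives no value for its high SD.

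**A tempting stronger reading.** A reader might infer that the plan expects work-ups unfinished at 6 or 12 months, and that 1% of such waits is what breaks the power claim. The documents do not support this.

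- Section E.2.2 says only that "Chart abstractions conducted at six months or 12 months follow-up may identify patients for whom recommended care has not yet been received". That is a statement of possibility in a risk section, and recommended care can include treatment, which lies outside the primary interval.
- A patient who never resolves has no interval to add to the SD. No passage says that anyone resolves at about 180 days.
- The 1% and the 150 days are assumptions.
- That every row fails at 1% depends on holding the ICC fixed. If between-clinic variance is fixed instead (0.01 × 225 = 2.25), the ICC falls to 2.25 / 447.75 = 0.005. The best row then becomes 800 / 1.497 = 534 effective subjects with 86% power; the other five rows stay below 80%.
- The claim already fails in three rows with no tail at all.

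**Conclusion.** The concern holds in a limited form. On the plan's own inputs, the unqualified power claim is wrong for 5 days at effective sizes of 201, 161 and 121 (76%, 68% and 57%). The conservative direction of the ICC is stated backwards. Both conclusions rest on figures in the protocol alone.

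The remaining rows depend on an SD that the documents do not justify. With 6 to 8 clinics and the stated ICC range, no row reaches 80% for 5 days once the SD exceeds about 20. Whether the true SD is that large cannot be settled from the documents; the right-tail figures show only how little it would take. The 10-day difference is safe at SD 15 and in the 1% illustration.

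The results assume equal arms and the plan's effective-sample-size method. This is a misstated power claim. It does not show that the trial is too small.

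**What to change.** In D.4.7.b:

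1. Delete the unqualified statement that the desired power will be achieved, and the wording that treats low ICCs or design effects as conservative.
2. Restate power, and the difference detectable with 80% power, for the current 12 clinics and planned enrolment over the ICC range of 0.01 to 0.04. Use one enrolment figure, reconciling the 600 to 800 here with the ceiling of 1,600 in E.1.1.
3. Take the mean, SD and shape of the interval from the roughly 700 baseline charts that D.3.3 already assigns to confirming sample size, in place of the supposed Normal(30, 15). Name the difference to which each power figure refers.

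The cost is a rewritten paragraph and a short calculation on data already being abstracted. No extra patients are needed. The downside is a less favourable stated power for 5 days.

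Moving the primary test to log days is not part of this fix. It would change the effect from a difference in mean days to a ratio. It would also run into intervals of zero days, which the date definitions in D.4.7.a appear to allow.

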###### **D.4.3 Patient Recruitment**

As described previously, seven clinics will provide the Navigator Program and five clinics will not provide the Navigator Program based on random assignment. A description of the Navigator Program to be provided at those clinics randomized to this condition follows. We will make no attempt to alter the delivery of services at those clinics not randomized to deliver the Navigator Program. Rather, we will use both observational and survey methods to characterize the processes that typically occur in these clinics once patients are identified as having a breast or colorectal abnormality. These data will be used to characterize the extent to which delivery of care differed in our two intervention conditions.

The eligibility criteria were defined in D.2.1 above. Subjects having cancer-related abnormalities will be identified by research assistants using a variety of methods. Methodologies for identifying patients will be refined and pilot tested in the project’s first year. Procedures for subject identification and recruitment will be identical for intervention and control clinics. Once identified, patients will be contacted by research assistants for recruitment into the study. Research assistants will use the following sources to identify patients:

*Appointment records*: Appointment records provide the reason for each patient’s visit and will be assessed weekly by research assistants. This information will be used to identify cancer related symptoms (i.e. breast lumps, rectal bleeding).

*Screening logs*: Participating clinics maintain screening logs to document completion of cancer screening tests such as Pap smears, mammograms, and FOBT. Research assistants will track screening logs on a weekly basis to identify patients having abnormal results on mammography or FOBT.

*Referral coordinators*: Research assistants will also make at least weekly contact with referral coordinators at each clinic to identify patients who may have been referred for cancer related problems.

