**E. Human Subjects Research.**

**E.1. Protection of Human Subjects.**

*E. 1.1.Human Subjects Involvement and Characteristics.--*

We are proposing a five-year project to develop and evaluate an appropriate and effective Navigation Program according to timeliness to diagnosis, appropriateness of care, satisfaction and quality of life. The study will be conducted at community-based centers/clinics that focus on serving medically populations. These sites include the Suncoast and Tampa Bay Community Health Centers (both federally qualified clinics) and Tampa General Hospital ambulatory clinics (public hospital). Subjects will be enrolled at both control and intervention sites. The research project will not affect the standard medical care that patients will receive. The intervention will only change the manner in which follow-up is provided, that is, adding a focused cancer navigator to the array of resources and outreach services that currently exist at these community-based centers. Control site practices will continue their usual efforts to promote tracking and follow-up of abnormalities and as part of this project, all sites will receive the Patient Navigation Program once it has been initially evaluated.

There are three phases to this study. In Phase I, a maximum of 70 subjects will be enrolled in focus groups or in-depth interviews and an anticipated 700 charts will undergo abstraction for baseline de-identified data. In Phase II, at most 1600 will be enrolled. In Phase I, information from patients’ medical records will be used to determine baseline data. For this reason, IRB and HIPAA issues are relevant for patients whose medical records are randomly chosen for review. We will request from the IRB a waiver of informed consent for medical record review and similarly a waiver of HIPAA authorization for medical record review in Phase I. We believe the project meets the four conditions necessary for waiving informed consent (45 CFR 46.116 (d) for this aspect of the study (chart review).

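### The power statement treats low ICC as the conservative case and claims adequate power without conditions, which the plan's own table supports for a 10-day difference at SD 15 but not for 5 days or a high SD

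*Protocol*

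**What the plan says.** All power text is in Protocol section D.4.7.b. The calculation is for the primary outcome, time from the abnormal finding to definitive diagnosis, treated as normal. On the control mean it says: "For the control group, the mean value of LOT was set up as 30.0" (days). On the method: "The required minimum sample size to achieve 80% statistical power is calculated based on the t-test", "with a significance level of 0.05 using a one-sided two-sample t-test".

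Two worked examples follow, both at SD 15. A 10-day difference needs 29 per group (58 in total). For a 5-day difference, "one would need at least 112 samples for each group (total 224"). Neither is named as the target difference.

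The section then allows for clustering, with 6 or 8 clinics of about 100 patients and ICC from 0.01 to 0.04. The table of effective sample sizes runs from 402 down to its last row, "6 | 600 | 0.04 | 4.96 | 121". The section calls 600 to 800 patients the expected size and concludes that power will be achieved "even under the most conservative conditions (low design effects or ICC values, and relatively high population standard deviation").

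Elsewhere the design is larger. Section D.2 reports 12 randomised clinics, section D.4.3 says "seven clinics will provide the Navigator Program and five clinics will not provide the Navigator Program based on random assignment", and section E.1 says "In Phase II, at most 1600 will be enrolled".

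**The concern.** Two things in the concluding sentence conflict with the table it summarises. First, it names low ICC and low design effect as the demanding conditions, when these are the easy end of the range. Second, it gives one blanket assurance, although the section's two examples differ nearly fourfold in required size (58 and 224) and some tabulated effective sizes lie between them.

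This is the protocol's only power justification for the primary outcome of a group-randomised trial. A reader who trusts the sentence could take a null result as evidence against a 5-day benefit when the plan's own figures do not support that. The table also no longer describes the trial as randomised, so nobody can read the actual power from it.

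**Working it through.** **Inputs.** From D.4.7.b: one-sided alpha 0.05, target power 80%, SD 15, differences of 10 and 5 days, 100 patients per clinic, 6 or 8 clinics, ICC 0.01 to 0.04. From D.4.3: 7 versus 5 clinics. Assumptions: equal arms for the 6- and 8-clinic rows, 100 per clinic for the 12-clinic layout, and every SD above 15 (Figure 1, which shows the SD range, was not available in the text reviewed).

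**Step 1: reproduce the plan's figures.** A one-sided two-sample t-test (noncentral t) gives 29 per group for 10 days (power 80.6%) and 112 per group for 5 days (80.0%). Design effect = 1 + (100 − 1) × ICC = 1.99, 2.98 and 4.96. Effective N = total / design effect, for example 600 / 4.96 = 121. All six rows reproduce.

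**Step 2: direction of ICC.** As ICC rises from 0.01 to 0.04, effective N falls from 402 to 161 (8 clinics) and from 302 to 121 (6 clinics).

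**Step 3: power in each row.** Noncentrality = difference / (SD × √(1/a + 1/b)), where a and b are the effective arm sizes. For effective N 121 and 5 days: 5 / (15 × √(2/60.5)) = 1.83. The one-sided critical value is 1.66 with patient-level df (119) and 2.13 with clinic-level df (6 − 2 = 4), giving power of 57% and 45%. All rows at SD 15:

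| Clinics | ICC | Effective N | 5 days, patient df | 5 days, clinic df | 10 days, patient df | 10 days, clinic df |
|---|---|---|---|---|---|---|
| 8 | 0.01 | 402 | 95% | 90% | >99% | >99% |
| 6 | 0.01 | 302 | 89% | 77% | >99% | >99% |
| 8 | 0.02 | 268 | 86% | 78% | >99% | >99% |
| 6 | 0.02 | 201 | 76% | 62% | >99% | 98% |
| 8 | 0.04 | 161 | 68% | 59% | 99% | 98% |
| 6 | 0.04 | 121 | 57% | 45% | 98% | 91% |

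Three rows are below 224 and below 80% for 5 days. With clinic-level df, five of the six are below 80%.

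**Step 4: a higher SD.** At effective N 121 and 10 days, the largest SD that keeps 80% power is 10 / ((1.645 + 0.842) × √(4/121)) ≈ 22. With patient-level df, power is 86%, 71% and 57% at assumed SDs of 20, 25 and 30.

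**Step 5: the layout as randomised.** With 7 versus 5 clinics of an assumed 100 each, effective N is 1200 / 1.99 = 603, 1200 / 2.98 = 403 and 1200 / 4.96 = 242. With 12 − 2 = 10 df (critical value 1.81), for ICC 0.04 and 5 days: a = 700 / 4.96 = 141.1, b = 500 / 4.96 = 100.8, noncentrality = 5 / (15 × √(1/141.1 + 1/100.8)) = 2.56, power 77%.

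| ICC | 5 days, SD 15 | 10 days, SD 15 | 10 days, SD 25 (assumed) |
|---|---|---|---|
| 0.01 | 98% | >99% | >99% |
| 0.02 | 92% | >99% | 98% |
| 0.04 | 77% | >99% | 89% |

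With patient-level df, the ICC 0.04 figure for 5 days is 82%.

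**The case against.** The strongest defence is that 224 is not a requirement. It belongs to one of two illustrations, the plan fixes no target difference, and the other illustration (58) is met in every row, with power of at least 98% by the plan's own method and 91% in the worst row with clinic-level df. This stands, and it limits the shortfall to 5 days or to a high SD. It does not rescue the sentence, which is unconditional and expressly includes a relatively high SD.

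A reader might infer three stronger points that the documents do not support.

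- *The trial as randomised is underpowered because the table covers too few clinics.* The 6-to-8 range is introduced as a precaution against losing clinics. Twelve clinics raise power: at an assumed 100 each, every effective N exceeds 224. What remains is that the table and its expected 600 to 800 patients are out of date.
- *One-sided powering contradicts the two-sided log-rank test of the same interval.* D.4.7.b places the log-rank comparison among exploratory secondary analyses, and the one-sided basis is stated consistently for the primary calculation. There is no contradiction.
- *The arithmetic is wrong.* It is not; every stated size, design effect and effective N reproduces.

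Clinic-level degrees of freedom may be handled in an analysis plan not seen here. They are used above as a refinement; the finding stands without them.

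**Conclusion.** The point holds in this form. The sentence reverses the role of ICC, and its blanket power claim is not supported by the table it rests on. For 5 days at SD 15, one-sided power is 76%, 68% and 57% in the three rows below 224 (62%, 59% and 45% with clinic-level df and equal arms). For 10 days at SD 15 the claim is sound in every row; at effective N 121 it fails once SD passes about 22. That threshold is computed, but whether the plan's SD range reaches it depends on Figure 1.

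For the 12-clinic layout, at an assumed 100 per clinic and SD 15, 10-day power exceeds 99% and 5-day power is 77% to 98% with clinic-level df. So this is a wrong and outdated power statement. It does not show that the design is inadequate, and no estimate or planned analysis changes.

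**What to change.** In D.4.7.b:

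1. Name high ICC or design effect, together with high SD, as the conservative case.
2. Replace the table with one for 7 versus 5 clinics, a stated number per clinic, ICC 0.01 to 0.04 and clinic-level degrees of freedom. Bring the expected total into line with section E.1. Spreading the 1600 ceiling evenly gives 1600 / 12 ≈ 133 per clinic, but that is an assumption and should be labelled as one.
3. Replace the blanket claim with power stated by difference and SD, and say which difference is the target. At an assumed 100 per clinic, SD 15 and one-sided 0.05, the figures are 98%, 92% and 77% for 5 days at ICC 0.01, 0.02 and 0.04, and over 99% for 10 days. Also show the higher SDs from Figure 1; for example, 10 days at an assumed SD of 25 and ICC 0.04 gives 89%.

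The cost is a rewritten paragraph and table, and a less favourable stated power for 5 days. No extra patients or clinics are needed.
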